#### Secondary analyses

All secondary outcomes will be compared between groups. T-test for independent samples and non-parametric tests will be used for continuous and categorical data, respectively. Further explorative analyses will be carried out on primary and secondary outcomes in subgroups of participants identified by strata used in randomization procedure. The statistical methods adopted for primary and secondary analyses will be used. All analyses will be under the expert supervision of the partner SAP.

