#### Primary

Changes from pre- $$({T}_{pre})$$ to post- $$({T}_{post})$$ treatment in GRASSP somatosensory scores of bilateral arms (12 is the maximum score for each side, equal to physiological condition) [32] are the primary outcome measure of the trial. Those changes will be computed assessing the difference between $${T}_{post}$$ and $${T}_{pre}$$ scores, or by computing the effectiveness, defined as the ratio between $${T}_{post}$$-$${T}_{pre}$$ difference and the maximum possible improvement for that specific scale, expressed in percentage.

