### Randomization procedure and methods

The random allocation sequence of participants to experimental (BCI-MI training) or control (Control-MI training) intervention groups will be generated by using Matlab (The MathWorks Inc, Natick, Massachusetts, USA, release 2019a).

The randomization sequence will be stratified by age (2 categories: ≤ 50 years old and > 50 years old) [61] and by GRASSP somatosensory scores (2 categories: ≤ 8 and > 8). A 1:1 allocation ratio will be used. For each stratum, the sequence will include 30 random allocations. The allocation sequence is securely stored at FSL. Randomization of participants will stop after randomization of the 30th participant in the study by summing participants in all strata.

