### Statistical analysis

#### Primary analyses

Baseline characteristics will be described by summary statistics for each group (experimental and control intervention). Differences between groups at baseline $${T}_{pre}$$ will be tested to check that the groups do not differ statistically at baseline.

The primary analysis will be performed in per protocol (PP) population on GRASSP somatosensory score changes between $${T}_{pre}$$ and $${T}_{post}$$. The PP will include all randomized participants who will perform (minimum) 12 training sessions. T-test or Wilcoxon Mann–Whitney rank test for independent groups will be used to compare continuous and discrete outcome measures respectively. Statistical significance will be assessed by two-tailed test.

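### The two-group tests planned within randomisation strata cannot show whether the treatment effect differs between strata; add an interaction estimate with its confidence interval (minor)

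*Protocol article*

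**What the plan says.** The Secondary analyses section of the protocol article announces the subgroup work: "Further explorative analyses will be carried out on primary and secondary outcomes in subgroups of participants identified by strata used in randomization procedure". The next sentence sets the method: "The statistical methods adopted for primary and secondary analyses will be used".

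The methods referred to are these:

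- Primary analyses: "T-test or Wilcoxon Mann–Whitney rank test for independent groups will be used to compare continuous and discrete outcome measures respectively", with "Statistical significance will be assessed by two-tailed test".
- Secondary analyses: "T-test for independent samples and non-parametric tests will be used for continuous and categorical data, respectively".

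The strata come from the section on randomisation procedure and methods. There are two age categories, cut at 50 years, and two categories of GRASSP somatosensory score, cut at 8. Recruitment stops at the 30th participant summed over all strata, and no minimum per stratum is given. The article names no treatment-by-stratum interaction.

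**The concern.** The usual reason to split a trial by age and baseline score is to see whether the treatment works better in some patients than in others. A two-group test inside one stratum estimates the effect in that stratum. It does not estimate the difference between two such effects, and a pair of p-values does not supply it either. Significance in one stratum and not in the other is a common result when the true effect is the same in both, because each stratum has only about half the patients and low power.

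At stake is the reading of the exploratory results. A statement that the training helps only younger patients, or only those with low baseline sensation, could rest on chance alone. The same tests are to be run on all secondary outcomes, which gives further occasions for such a pattern.

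**Working it through.** **Inputs.** From the Sample size section: 15 per group, alpha 0.05, one-tailed t-test, 80% power. From Primary analyses: two-tailed testing. From the randomisation section: 1:1 allocation, two binary factors, 30 participants in total. Assumed, because the article does not give them: the effect size, the stratum sizes, normally distributed outcomes with a common SD, and all 30 participants analysed.

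**Step 1: the plan's own figure.** The 15 per group cannot be reproduced, since no effect size or SD is stated. It can only be inverted. With noncentrality d × √(15 × 15 / 30) = 2.739 d and 28 degrees of freedom, one-tailed power of 80% at 0.05 requires d = 0.931. This is an assumption from here on. It comes from a calculation based on upper extremity motor scores, whereas the primary outcome is a sensory score.

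**Step 2: power within a stratum.** Two strata of 15 are taken, one with 8 versus 7 and the other with 7 versus 8. Noncentrality is d × √(8 × 7 / 15) = 1.932 d, with 13 degrees of freedom, two-tailed 0.05. At d = 0.931 the noncentrality is 1.80 and the power p is 0.384.

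**Step 3: chance that the two strata disagree under a uniform effect.** The strata are independent, so P(one significant, the other not) = 2p(1 − p).

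| True d, same in both strata | Power per stratum | 2p(1 − p) |
|---|---|---|
| 0 | 0.050 | 9.5% |
| 0.5 | 0.146 | 24.9% |
| 0.8 | 0.299 | 41.9% |
| 0.93 | 0.384 | 47.3% |
| 1.06 | 0.475 | 49.9% |

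The last row is the effect that 15 per group would detect with 80% power in a two-tailed test.

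**Step 4: the interaction test on the same data.** A uniform effect cancels from the difference between the two stratum effects, so the test keeps its 5% level. In 20,000 simulated trials it rejected in 5.1% at d = 0 and 5.2% at d = 0.93. The within-stratum tests disagreed in 9.7% and 47.4% of the same trials.

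**Step 5: sensitivity to the split, at d = 0.93.** Strata of 20 and 10 disagree in 50% of trials, and strata of 24 and 6 in 56%. If the subgroups are the four crossed cells of 7 to 8 patients, power per cell is 17% to 20% and the cells are not all in agreement in 56% of trials. Where a rank test is used in such cells, an exact two-tailed test cannot reach 0.05 with 4 versus 3 (smallest p = 2/35 = 0.057) or 3 versus 3 (2/20 = 0.10).

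**Step 6: precision of the interaction.** Its standard error is √[2 × (1/8 + 1/7)] = 0.73 SD. With 26 residual degrees of freedom the 95% CI is about ±2.06 × 0.73 = ±1.5 SD. Power for a true difference of 0.93 SD between strata is about 23%.

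**The case against.** The strongest reply is that the harm depends on an inference that the article does not make. The analyses are labelled explorative, the stated aim of the trial is overall superiority, and a two-group comparison within a stratum is a valid estimate for that stratum. This stands, and it limits the point to a risk of misreading.

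A reader might infer that the investigators chose against an interaction test, or intend to claim a differential effect from contrasting p-values. The text supports neither. It names methods that contain no interaction and says nothing about how the subgroup results will be interpreted.

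A reader might also infer that patients in the upper GRASSP stratum have little room to improve, because "12 is the maximum score for each side". The article does not say whether the cut at 8 applies per side or to both sides together. On a 24-point sum, a patient scoring 9 could still gain 15 points. The primary outcome may also be expressed as a share of the maximum possible improvement, and an interaction on raw change would not remove a ceiling in any case. That argument is not relied on here.

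A full analysis plan may add an interaction. An article may leave such detail out, but here it states a method, and that method does not do the job.

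Finally, the interaction would itself be imprecise and would leave real heterogeneity unresolved. That is true. It is a reason to report an interval that shows the uncertainty, since separate p-values hide it.

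**Conclusion.** The point holds as a minor one. The stated subgroup method cannot estimate whether the effect differs between strata. Were differing significance read as a differential effect, a uniform true effect would produce that pattern in 9.5% to about 50% of trials per factor and outcome, for d from 0 to 1.06. An interaction test would err in about 5%. The contrast is only about twofold if there is no effect at all, fivefold at d = 0.5, and about ninefold at d = 0.93.

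These figures assume normal outcomes, t-tests, 30 analysed participants and, in the main table, two equal strata. The value 0.93 is inferred from the sample size and is not stated in the article. The primary comparison and its conclusion are not touched.

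**What to change.** Replace the sentence on subgroup methods with the following elements.

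- For each stratification factor, fit one model to all analysed participants with treatment, the factor and their interaction, and report the interaction estimate with its 95% CI.
- Show the within-stratum treatment estimates with CIs descriptively, without p-values.
- State that these analyses are exploratory and that the interaction is imprecise with 30 participants: a 95% CI of about ±1.5 SD, and power of about 23% for a difference of 0.93 SD.

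The cost is wording only; recruitment, data collection and the primary analysis do not change. The price is that there are no subgroup p-values to quote, and that a linear model stands beside the rank test planned for discrete outcomes, so its exact form should be fixed in advance.

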### Data collection and management

An ad hoc CRF is implemented for all type and timing assessments.

Specifically, the CRF will consist of two sections:

i) the “Baseline and Randomization Section” which will contain each participant demographic, neurological and clinical data and all data collected for the screening section including the Informed Consent, the assigned randomized treatment, and the assessment before intervention ($${T}_{pre}$$). This part will be filled in by unblinded personnel.

ii) the “Outcome and Training Section” which will not include data on assigned experimental treatment but will contain all the outcome collected in each training session and during the assessment after intervention ($${T}_{post}$$). It will be filled by blinded personnel, namely the outcome assessors.

A specific standard operating procedure including time schedule, and instruction for management and compilation of the CRF will be used. All study staff responsible for outcome assessment (neurologists, neuropsychologists, neurophysiologists, therapists, neuroimaging researchers and other researchers involved) and training (therapists and EEG technicians) will be trained on procedures to ensure validity and reliability of trial data collection.

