**Fig. 1 Fig1:**
[figure not shown]
DiSCIoser Randomized Controlled Trial summary. All Spinal Cord Injury (SCI) patients admitted to the Spinal Unit at Fondazione Santa Lucia IRCCS will be screened (T enrol) for eligibility according to Inclusion/Exclusion criteria. The evaluation according to the International Standards for Neurological Classification of SCI (ISNCSCI) ASIA Impairment Scale (AIS) and the predicted mean Upper Extremity Motor Score (UEMS) recovery will be used for eligibility. Eligible participants will be presented with the Informed Consent and recruited (30 participants). Clinical, neuropsychological, neurophysiological and neuroimaging assessments will be performed before (T pre) and after (T post) the intervention

The primary outcome is the Graded Redefined Assessment of Strength, Sensibility and Prehension (GRASSP) somatosensory sub-score [32]. Secondary outcomes are the GRASSP motor sub-score, the self-care section of the Spinal Cord Independence Measure (SCIM) [33] scale and a battery of clinical/functional scales (See Table 1 for details) to monitor upper limb muscle strength, tone, pain, and functional ability. Other pre-specified outcome measures are extracted from neuropsychological, neurophysiological and neuroimaging assessment before and after training. The overall outcome assessments are detailed in the Assessment section. The outcome assessors are blinded to the treatments.

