### Assessments

#### Outcome assessments

Outcome measures refer to the assessments that will be conducted both before and after intervention. The evaluation timepoints are:

$${T}_{pre}$$ at randomization, before intervention.

$${T}_{post}$$ at the end of the intervention.

(See the SPIRIT diagram in Table 1 for details).

Trained clinical/research staff neurologists, neuropsychologists, neurophysiologists, therapists, and radiologists will perform the assessments and will be blind to the participant intervention allocation except for recruiting neurologists who are not blinded and do not participate to the assessment. Data will be recorded in an ad hoc Case Report Form (CRF; details in Data collection and management section).

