### Intervention

#### Dosage of intervention training

Both BCI-MI and Control-MI training will be completed in 12 weeks with a weekly frequency of 3 sessions per week, lasting 45 min. Treatment adherence is set at 12 of the 36 intervention training sessions. We do not expect the BCI-MI and Control-MI interventions to cause adverse effects (non-invasive procedure; no drug-administration; no adverse events [30]) and both intervention deliveries will be under the care of SCI specialized personnel (physiotherapists, neurophysiology technician experts in patient EEG recordings). To monitor any possible deviation from the intervention training protocols (e.g., missing sessions for intervening illness), a report form for each participant will be compiled at each planned training session by the training personnel and it will be part of the CRF (CRF- Training section; details in Data collection and management section). The study interventions are conceived as add-on to the standard rehabilitation care (treatment as usual; TAU), and both groups will receive the same dosage of TAU and add-on training. To ensure comparability between and within group, TAU will be delivered according to an equal intensive regimen for both groups. The intensive regimen includes neuromotor physiotherapy sessions of 40 min each, twice a day, except on Saturdays, when it is once a day, for 6 days a week.

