#### BCI-assisted motor imagery training (BCI-MI, experimental intervention)

An all-in-one BCI-supported MI training station (Fig. 2) developed considering the requirements and specific needs of patients with cervical SCI, will allow to practice the kinesthetic MI of hand closing and opening in a closed-loop condition. To further engage patients during the MI training, and to make it more appealing, the BCI station also includes the option of performing the MI of goal-oriented movements. For example, the hand opening or closing will allow the patient to burst soap bubbles, move billiard balls, and turn on/off light bulbs within a virtual environment. Therapists will choose on a session-by-session basis whether to use animation and also which type in order to introduce variation in the training. The type of animation used in each session will be recorded on the specific training CRF.

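### The CRF completion rules conflict with one another and, as written, put assessor blinding at risk

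*Protocol article*

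**What the plan says.** All references are to the protocol article.

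- **Blinding rule.** Study design (text under Fig. 1) states: "The outcome assessors are blinded to the treatments". Outcome assessments, which covers both time points, says that those performing assessments "will be blind to the participant intervention allocation except for recruiting neurologists who are not blinded and do not participate to the assessment".
- **First CRF part** (Data collection and management). Besides screening and consent data it contains "the assigned randomized treatment, and the assessment before intervention", and "This part will be filled in by unblinded personnel".
- **Second CRF part** (same section). It omits the assigned treatment but holds the outcomes collected at each training session and the post-intervention assessment. On who completes it: "It will be filled by blinded personnel, namely the outcome assessors".
- **Training record.** Dosage of intervention training says that "a report form for each participant will be compiled at each planned training session by the training personnel". It places this form in the CRF training section and refers the reader to Data collection and management for details.
- **Animation.** The section on BCI-assisted motor imagery training says: "The type of animation used in each session will be recorded on the specific training CRF". The section on motor imagery training without BCI support describes a hand that does not move.

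**The concern.** The trial is single blind. Staff who deliver the training know the arm. The primary outcome is a pre-to-post change in a clinician-administered sensory score with a maximum of 12 per side, in 30 participants. Blinded assessment is the main stated safeguard against detection bias.

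The CRF rules weaken that safeguard in two places. First, assessors are assigned the part of the CRF that, by the article's own cross-reference, also seems to hold the trainers' session reports, and those reports carry an item that points to the arm. Second, pre-intervention results are kept with the allocation, on a form completed by people who know it. An assessor who looks up a baseline value there would see the arm. An assessment made with the arm known cannot be re-blinded afterwards, so the forms need to be right before use.

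**Working it through.** No arithmetic applies. The point rests on setting the statements side by side.

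**Step 1: who completes the training part of the CRF?**

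| Section | Form | Completed by |
|---|---|---|
| Dosage of intervention training | Session report, in the CRF training section | Training personnel |
| Data collection and management | Combined outcome and training part | Blinded outcome assessors |

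The first section sends the reader to the second for details, so both appear to describe the same part of the CRF. They name different people, and the training personnel necessarily know the arm.

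**Step 2: does that part reveal the arm?** The allocation is explicitly left out. The animation type, however, goes on the training CRF. Animated goal-oriented tasks are described only for BCI-MI, where the therapist chooses session by session whether to use one. In Control-MI the displayed hand is static. A filled animation entry therefore points to BCI-MI. This is an inference from two sections; no single sentence says that animation is exclusive to BCI-MI.

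**Step 3: who records the pre-intervention assessment?** Outcome assessments has blind assessors at both time points and says of the only unblinded clinicians, the recruiting neurologists, that they are the exception: "except for recruiting neurologists who are not blinded and do not participate to the assessment". Data collection and management has the pre-intervention assessment entered by unblinded personnel, in the part that also shows the assigned treatment. Taken literally, the two conflict.

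**Step 4: can knowledge of the arm affect the baseline values?** Randomization procedure and methods stratifies by GRASSP somatosensory score (8 or below, above 8). That score must exist before a participant can be placed in a stratum, so the assigned arm cannot have influenced it. The other baseline measures are timed only as at randomization and before intervention, so nothing in the text guarantees that they precede disclosure of the arm.

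**Step 5: is there a stated access barrier?** Confidentiality limits file access to the centre's staff involved in the study. That group includes the assessors, and no restriction by role is given.

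**The case against.** The strongest reply is that this is loose wording and not a breach. The second CRF part is said to contain outcomes from each session, and such outcomes exist: motivation, mood and satisfaction ratings. One can picture outcome sheets completed by assessors and a separate training log completed by trainers, with animation type only on the log. The allocation is deliberately kept out of the assessors' part. Completing a form may mean transcription and not assessment. A CRF standard operating procedure is mentioned but not shown, and a journal article would normally leave form layout to it.

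Much of this stands. A reader might infer that assessors will certainly see the arm at the post-intervention visit. The article does not support that: it does not say that the sheets are physically joined or that assessors handle earlier sessions' records.

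A reader might also infer that trainers assess their own participants, because therapists appear in both roles, or that the neurophysiologists who select BCI features also assess those participants. These are professions, not named individuals, and the blinding rule in Outcome assessments already excludes such overlap.

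The reply does not remove the conflict. The article does more than leave the layout open. It states who completes each part, and those statements disagree. A standard operating procedure that followed Data collection and management would carry the weakness into practice; one that departed from it would contradict the published protocol.

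**Conclusion.** The point holds as a conflict between four sections (Outcome assessments, Dosage of intervention training, BCI-assisted motor imagery training, and Data collection and management) that puts assessor blinding at risk. It does not show that blinding is broken.

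The combined outcome and training part is the more serious element, because it bears on post-intervention assessments in both arms. It rests on two assumptions: that animation is used only in BCI-MI, and that the trainers' report belongs to the CRF part that assessors complete, as the cross-reference suggests.

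The baseline element is weaker. Its effect on the primary outcome is likely small because the GRASSP somatosensory score must be obtained before allocation. What remains is the lack of that protection for other baseline measures, and the exposure of anyone who consults baseline scores on a form showing the arm.

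The size of any bias cannot be estimated. The article gives no standard deviation for GRASSP change, and its sample size rests on a different scale (UEMS), so any figure in SD units would be assumption only.

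**What to change.** Split the CRF into three forms:

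1. Screening, consent and allocation, completed by unblinded personnel.
2. Pre- and post-intervention outcomes, recorded only by blinded assessors, with the pre-intervention assessment completed before the allocation is revealed.
3. A training log, including animation type, completed by training personnel and not accessible to assessors.

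Then reconcile the wording of Outcome assessments, Dosage of intervention training, BCI-assisted motor imagery training, and Data collection and management, so that each form has one stated group completing it.

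The cost is a re-cut of the paper CRF and a revision of its standard operating procedure. Existing staff can do the work, and no new assessment or study procedure is needed.
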